### Trial design

The current study is a randomized controlled trial with two active conditions (CBITS vs. TAU +) and three measurement time points. An independent institution (Institute of Epidemiology and Medical Biometry, Ulm University) will perform the randomization. The randomization will be conducted within each child welfare program. Hence, half of the participants within the program will be in the CBITS condition and the other half will be in the TAU + condition. Randomization will be done in the group of registered participants as CATS-2-stratified block randomization using the randomization software ROM [25]. Participants will be randomized in either CBITS or TAU + after their agreement to participate in the study and after the screening (T0) of participants of the respective facility is completed. The participants and their CATS-2 severity score will be reported as a list and will be sent to the Institute of Epidemiology and Medical Biometry for randomization. See Fig. 1 for participant flow through the study.

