### Sample size

Based on the literature and our planned analyses on the effectiveness of CBITS for children, we expect a moderate effect size of *d* = 0.7 for the CBITS intervention. An attempt was made to estimate the likely effect size based on longitudinal studies reporting on children and adolescents living in the child welfare system: In our own trial of unaccompanied refugee minors, we found an effect size of *d* = 0.15 for routine care in child welfare programs [18]. A Swiss study investigating externalizing behavior problems in institutionalized adolescents over the course of 1 year found effects of *d*_girls_ = 0.28 and *d*_boys_ = 0.24 [19]. Another study investigating emotional and behavioral symptom trajectories of children in long-term out-of-home care in an English local authority found that the largest trajectories were chronic symptom profiles, in which young people were rated in the abnormal range from their first year in care and remained in this range (based on the descriptive statistics reported we calculated *d* = 0.02–0.1 for emotional problems [20]). Based on these studies, we assume a mean effect size of *d* = 0.1 for routine care for children in child welfare programs. As children and adolescents randomized to TAU + will also receive a report with a treatment indication, we assume that a small proportion in TAU + condition (10–20%) will find their way to local service providers. For those receiving psychotherapeutic treatment from local service providers, we assume a mean effect size of *d* = 1.0 based on therapy as usual conditions in other trials (e.g., [21]). In sum, based on the before-mentioned literature on routine care in child welfare systems and the assumption that a small proportion will receive treatment at local service providers, we assume an overall mean effect size of *d* = 0.3 for the TAU + condition. Following the expected effect size of *d* = 0.7 for CBITS and *d* = 0.3 for TAU + , we assume a controlled effect size of *d* = 0.4 between conditions at 4-month follow-up (T1) in favor of CBITS on the primary measure of PTSS (CATS-2). A power analysis conducted with G*Power for the within-(time)-between-(condition)-interaction requiring a power of 0.80 and *α* = 0.05 (two-tailed), a correlation of *r* = 0.3 among replicated measures (based on our previous own RCTs [18, 22]) estimates a sample size of *N* = 72 (*n* = 36 per condition) to detect the controlled effect size of *d* = 0.4 for the primary outcome between conditions. With an assumed dropout rate of about 20% across both conditions, an oversampling of *n* = 18 participants is needed, resulting in an overall sample of *N* = 90 participants (*n* = 45 per condition; *n* = 22–23 per participating site).

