### Statistical analysis

The primary outcome (CATS-2 self-report) will be analyzed using mixed effects models (MEM) with fixed effects of group (CBITS vs. TAU +) and time (baseline T0 versus 4-month follow-up T1) as well as their interaction (*α* = 0.05). Based on the longitudinal design of the data structure, data will be nested by participants; and repeated measures will be modeled using an unstructured covariance matrix. Since MEMs can handle missing data within the longitudinal data structure, the analyses will be performed with the ITT sample including all randomized participants (*N* = 90). We will use exploratory MEMs for the secondary outcomes. Additionally, per-protocol analyses will be performed for all outcomes.

We could identify several factors that might be related to dropout in children who receive trauma-focused treatment such as number of traumatic events (e.g., [35]). Hence, we will run a sensitivity analysis with the following variables: child age and gender, pre-treatment PTSS level, number of traumatic events, and type of treatment. In more detail, we will run the analysis while controlling for these potential covariates, repeat the analysis not controlling for the factors, and check for differences in the results. When finding the differences, we will use the model with the covariates to allow for making the assumption of missing at random for an unbiased effect estimate. Accounting for non-compliance is not necessary for the ITT analyses. For the per-protocol analyses, we will adjust for possible covariates for non-compliance in order to assume strong ignorability plausible. Effect sizes will be calculated by Cohen’s *d* [36]. A significance level of *α* = 0.05 will be used. Exploratory subgroup analyses for known PTSS outcome predictors (e.g., age, sex, baseline PTSS) will be performed. Safety: We will compare the frequency of SAEs between conditions using the *χ*^2^ tests (*α* = 0.05). No interim analyses will be performed on the main outcomes.

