In general, treatment and the associated processes of change and diagnostic procedures may be evaluated as stressful by the participant [38]. Therefore, symptoms may temporarily worsen. In the context of CBITS, the development of a trauma narrative can be experienced as stressful as it involves direct confrontation with the traumatic experience and avoided stimuli. However, participants can directly benefit from successful treatment, and long-term symptom reduction can be achieved. Even for the TAU + group who will only have the possibility to receive CBITS after T_1_, we do not expect any safety issues as they can participate in any other medical or psychotherapeutic treatment during the trial. Study safety will be ensured by monitoring for the incidence of serious adverse events (SAEs; e.g., suicide attempts, unplanned hospitalizations, occurrence of life-threatening conditions) at all assessments. All such incidents and other aspects of study safety will be regularly reported to an independent Data and Safety Monitoring Board (DSMB), which offers advice on protocol changes in the event of such incidences, or even on discontinuation of the trial. In addition, study therapists participating in the study will report SAEs of a study participant they treat as soon as they gain knowledge about it (within two working days). Any SAEs occurring before, after, or between screening appointments will be reported by the child welfare project coordinators at the child welfare programs immediately (the latest within two working days). The study protocol will also include several standard operations of procedure (SOP) which will guide the study staff and therapists through the safety study procedures.

The study offers different incentives/compensations to the participants, the child welfare programs, and therapists for participation in the study.

An international advisory board with leading experts in the field of PTSD treatment for children and adolescents was established. Both the advisory board and the DSMB will hold online regular meetings with the study team and provide continuous advice during the trial.

The quality and completeness of all data will be continuously monitored by an independent data manager located at Ulm University, who will ensure that the trial is conducted and data are generated, documented, and reported, all in compliance with the study protocol, GCP guidelines, and other applicable regulatory requirements.

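### The only between-arm safety analysis stated is a chi-square test of SAE frequency; an SAE risk difference with a confidence interval would say more about harm at almost no cost

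*Protocol article*

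**What the plan says.** The Statistical analysis section gives the between-arm safety analysis in one sentence: "We will compare the frequency of SAEs between conditions using the" chi-square tests, with alpha = 0.05 in brackets. The section also sets a general threshold: "A significance level of *α* = 0.05 will be used". It names Cohen's d as the effect size measure but no measure or interval for the SAE comparison.

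The Sample size section plans for the CATS-2 outcome only, "resulting in an overall sample of *N* = 90 participants", that is 45 per condition. Under Trial design, "half of the participants within the program will be in the CBITS condition and the other half will be in the TAU + condition".

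Safety oversight is described elsewhere. The Ethical considerations, safety, and monitoring section says "Study safety will be ensured by monitoring for the incidence of serious adverse events", with suicide attempts, unplanned hospitalizations and life-threatening conditions as examples. It adds reporting within two working days and regular reports to an independent DSMB, which may advise changing or stopping the trial. The measures sections add a standardized SAE checklist for caregivers and the 18-item Children-INEP on unwanted effects of therapy, by self-report and by caregiver report. No expected SAE rate appears anywhere.

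**The concern.** A significance test returns one of two answers. With few events and 45 children per arm, it will usually return non-significance whether or not CBITS raises the SAE risk. Without an estimate and interval, the reader cannot tell whether the data exclude an important excess or are merely too sparse to show one.

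This matters because the article itself expects that symptoms may worsen for a time and that work on the trauma narrative can be stressful. It also aims to inform policymakers about wider use. A split of 5 children with an SAE under CBITS against 1 under TAU+ would be non-significant, although the data would be compatible with an excess of about 21 percentage points.

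The point does not depend on who reports SAEs or when. It would hold with complete reporting over equal periods.

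**Working it through.** **Inputs from the article.** Chi-square test, alpha 0.05 (Statistical analysis); 90 participants, 45 per arm, 1:1 (Sample size, Trial design). "With an assumed dropout rate of about 20% across both conditions" leaves about 36 per arm if children who drop out give no SAE data.

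**Assumption.** The control SAE risk is not given. I take 2%, 5% and 10%, and 20% as a high value. I count each child once, as with or without an SAE. The rate ratios of 2 and 3 are illustrative.

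**Step 1. The plan's own figure.** G*Power's within-between interaction uses lambda = f² × N × m / (1 − r). With f = 0.4/2 = 0.2, m = 2 and r = 0.3, N = 72 gives power 0.808 and N = 70 gives 0.796. Then 72 / (1 − 0.20) = 90. The stated N is reproduced on this entry of f. SAEs do not enter the calculation.

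**Step 2. What the test needs.** With x and y children with an SAE out of 45 per arm and t = x + y, the uncorrected statistic is X² = 90(x − y)² / [t(90 − t)], significant above 3.841.
- 5 vs 1: 90 × 16 / (6 × 84) = 2.86, p = 0.09.
- 4 vs 0: 90 × 16 / (4 × 86) = 4.19, p = 0.041. Fisher's exact test gives p = 0.117 for the same table.
- Smallest significant CBITS count: 4 if control has 0, 6 if control has 1, 8 if control has 2.

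**Step 3. Miss rates.** Miss rate = 1 − the sum, over all count pairs with X² > 3.841, of Bin(x; n, p₁) × Bin(y; n, p₀).

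| Control risk (assumed) | Doubling, 45 per arm | Tripling, 45 per arm | Doubling, 36 per arm | Tripling, 36 per arm |
|---|---|---|---|---|
| 2% | 95% | 87% | 97% | 91% |
| 5% | 84% | 61% | 87% | 68% |
| 10% | 72% | 31% | 78% | 42% |
| 20% | 44% | 2% | 53% | 5% |

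For 80% power at 45 per arm, the CBITS risk would have to reach about 18%, 25% or 33% at control risks of 2%, 5% or 10%.

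**Step 4. Adequacy of the approximation.** At 5% control risk, the expected count in each SAE cell is 45 × (0.05 + 0.10)/2 = 3.4 for a doubling and 45 × (0.05 + 0.15)/2 = 4.5 for a tripling. Both are below the customary 5. Fisher's test would miss more: 94% and 77% in these two cases.

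**Step 5. What an interval would show.** Newcombe's interval combines the Wilson limits (l, u) of the two proportions: lower = d − √[(p₁ − l₁)² + (u₂ − p₂)²], upper = d + √[(u₁ − p₁)² + (p₂ − l₂)²]. For 5 vs 1, the Wilson limits are 4.8% to 23.5% around 11.1%, and 0.4% to 11.6% around 2.2%. So d = 8.9 points, with limits −2.4 and +21.4.

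| CBITS vs TAU+ (of 45 each) | Risk difference | 95% Newcombe limits |
|---|---|---|
| 2 vs 2 | 0 points | −11 to +11 |
| 4 vs 2 | +4 points | −7 to +17 |
| 5 vs 1 | +9 points | −2 to +21 |

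All three tables are non-significant. Only the intervals show how much harm each leaves open.

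**The case against.** **The article draws no conclusion of safety from the test.** It states no safety claim, margin or decision rule, so a reader who infers that p > 0.05 will be reported as proof of safety goes beyond the text. This stands, and it is why the point is an improvement and not an error.

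**Safety does not rest on this test.** A reader might take it as the trial's only safety provision. That is wrong, given the DSMB, the two-day reporting, the checklist and the Children-INEP. These provisions serve monitoring of individual events and unwanted effects, however, and none provides a between-arm SAE estimate.

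**The miss rate is not a property of the design.** It is tempting to say that a two- to threefold rise is missed 60–85% of the time, but that range belongs to a control risk near 5%, which the article does not give. At 2% the miss rates are higher. At 10% a tripling is missed only 31% of the time, and at 20% almost never. Nothing in the article excludes a higher rate in this population. The figures can only be shown as a range.

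**Trials sized on a symptom score are not normally powered for SAEs, and reporting detail may sit in an analysis plan that is not shown.** The first part is accepted: no larger sample is asked for. The second carries less weight, because the article does fix the SAE method by naming the test and its alpha level. An unseen plan may already add estimates; if so, the article's sentence should be aligned with it.

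**Conclusion.** The point holds as a cheap improvement. The stated between-arm safety analysis is a bare chi-square test. With 45 per arm and assumed control risks of 2% to 10%, it misses a doubling of SAE risk 72–95% of the time and a tripling 31–87% of the time. When SAEs are uncommon, a non-significant result is therefore weak evidence about harm, and the chi-square approximation is itself doubtful at such counts.

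This rests on an assumed control risk, one SAE status per child and the uncorrected test. If SAEs are frequent (20% in control), the test detects a tripling well and the concern is much smaller. In either case, an estimate with an interval is more informative than the test alone.

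The article does not support the inferences that safety oversight is missing, that the sample size is faulty because it ignores SAEs, or that the investigators plan to claim safety from non-significance.

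**What to change.** In the Statistical analysis section, make estimation the main SAE analysis:
- report the number and proportion of children with at least one SAE in each arm;
- report the risk difference, CBITS minus TAU+, with a 95% Newcombe or exact confidence interval;
- base the safety statement on the upper limit, in the form that an excess above so many percentage points is excluded;
- label any p-value as descriptive, and say that non-significance will not be taken as absence of harm.

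This takes one or two sentences and needs no new data or participants. The price is a less favourable safety statement: with few events, the interval will typically not exclude an excess of about 10 to 20 percentage points.

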### Ethical considerations, safety, and monitoring

The study was planned and will be conducted in accordance with the International Council for Harmonization Guideline for Good Clinical Practice [37]. The trial is registered under ClinicalTrials.Gov (https://clinicaltrials.gov; registration number NCT06038357, date September 13, 2023). It has been approved by the ethics review board of Ulm University (November 27, 2023; Nr. 267/23 – FSt/Sta). All participants will be informed about the study in oral and written form, with details of the trial’s procedures, risks, costs, confidentiality, data storage, and about the right to discontinue participation at any time without giving any reasons. Participants will be free to continue any other treatment in case they quit the research program. Written informed consent will be obtained from all study therapists, caregivers, and participants (as well as from their parents/legal guardians) before study inclusion.

In general, treatment and the associated processes of change and diagnostic procedures may be evaluated as stressful by the participant [38]. Therefore, symptoms may temporarily worsen. In the context of CBITS, the development of a trauma narrative can be experienced as stressful as it involves direct confrontation with the traumatic experience and avoided stimuli. However, participants can directly benefit from successful treatment, and long-term symptom reduction can be achieved. Even for the TAU + group who will only have the possibility to receive CBITS after T_1_, we do not expect any safety issues as they can participate in any other medical or psychotherapeutic treatment during the trial. Study safety will be ensured by monitoring for the incidence of serious adverse events (SAEs; e.g., suicide attempts, unplanned hospitalizations, occurrence of life-threatening conditions) at all assessments. All such incidents and other aspects of study safety will be regularly reported to an independent Data and Safety Monitoring Board (DSMB), which offers advice on protocol changes in the event of such incidences, or even on discontinuation of the trial. In addition, study therapists participating in the study will report SAEs of a study participant they treat as soon as they gain knowledge about it (within two working days). Any SAEs occurring before, after, or between screening appointments will be reported by the child welfare project coordinators at the child welfare programs immediately (the latest within two working days). The study protocol will also include several standard operations of procedure (SOP) which will guide the study staff and therapists through the safety study procedures.

The study offers different incentives/compensations to the participants, the child welfare programs, and therapists for participation in the study.

An international advisory board with leading experts in the field of PTSD treatment for children and adolescents was established. Both the advisory board and the DSMB will hold online regular meetings with the study team and provide continuous advice during the trial.

The quality and completeness of all data will be continuously monitored by an independent data manager located at Ulm University, who will ensure that the trial is conducted and data are generated, documented, and reported, all in compliance with the study protocol, GCP guidelines, and other applicable regulatory requirements.

## Discussion

This study will be the first RCT on the effectiveness and implementation of a trauma-focused group intervention for traumatized children and adolescents in child welfare programs, which will be implemented outside of the clinical setting. As the included study participants constitute an especially vulnerable population for developing trauma-related disorders on the one hand, and oftentimes only have limited access to trauma-focused EBTs in Germany on the other hand, this study might provide crucial insights on how to improve their short- and long-term mental health. The study also aims to report on different implementation aspects of trauma-focused (group) interventions outside of routine clinical care and to potentially inspire future scientific efforts in documenting factors, facilitating the implementation of these interventions in settings in which children and adolescents already spend most of their time (schools, daycare, child welfare, etc.) and feel more comfortable in than in a clinical setting.

### Dissemination

The findings of this trial will be disseminated both within academia (i.e., scientific papers, presentations at conferences) and outside of academia (i.e., on a societal level). As there is currently no evidence for an outreach group treatment delivered by therapists in child welfare programs in Germany, one major dissemination goal of this study is to inform policymakers on the potential effectiveness and benefits of establishing such interventions long-term. The results of this trial will also be communicated to participants, therapists, and child welfare staff included in the trial and to larger therapist organizations and child welfare networks in Germany. With an open-access publication of the German version of the manual and other CBITS materials, we want to motivate other practitioners to consider offering the intervention after the study. The sustainable implementation of the CBITS intervention will enable trained therapists to implement trauma-informed care not only for study participants but also for non-participants. This trial will hopefully be able to model future translations of outreaching EBTs into regular clinical training programs and child welfare programs across Germany.

### Strengths and limitations

This study has several strengths: (1) By recruiting participants in several different child welfare programs in four different regions in Germany, we will endeavor to recruit a sample that is as representative as possible. (2) The project is aware of the challenges in the child welfare programs (e.g., staff turnover) and will seek to determine the facilities’ readiness to collaborate with mental health services. (3) By randomizing the participants within the child welfare programs and using the control condition TAU + where we document all (mental) health care offers to the participants, we aim to furnish reliable evidence of the actual care for children and adolescents cared for by the child welfare system in Germany. (4) This study claims a high external validity that represents the natural mental health and child welfare context in which children and adolescents in Germany normally reside. (5) The mixed-methods approach on assessment of feedback to the intervention by participants and therapists will allow us a high level of participant involvement.

Possible limitations to the trial are as follows: (1) Some measures will have to be translated to German and are therefore not validated in this language version. (2) The assessment only includes self-report questionnaires and no clinical interviews to ensure a high feasibility of the trial. We will not, therefore, be able to report on clinical diagnoses. (3) We believe that the child welfare programs participating in the trial will show a high motivation to improve mental health care for traumatized children and adolescents who cannot live with their (biological) parents that is probably beyond average. Additionally, therapists willing to participate may be particularly interested in providing EBTs, which could result in a selection bias.

